## Abstract

**Background:**

Participation in organised youth sports (OYS) has been recommended as an opportunity to increase young peoples’ moderate-to-vigorous physical activity (MVPA) levels. Participants, however, spend a considerable proportion of time during OYS inactive. The purpose of this study, therefore, was to investigate whether coaches who attended coach education sessions (where education on increasing MVPA and decreasing inactivity during training was delivered) can increase players’ MVPA during training sessions over a 5-day basketball program compared to coaches who did not receive coach education sessions.

**Methods/design:**

A convenience sample of 80 female players and 8 coaches were recruited into the UWS School Holiday Basketball Program in Greater Western Sydney, Australia. A two-arm, parallel-group randomised controlled trial was employed to investigate whether coaches who attended 2 coach education sessions (compared with a no-treatment control) can increase their players’ MVPA during training sessions over a 5-day basketball program. Objectively measured physical activity, directly observed lesson context and leader behaviour, player motivation, players’ perceived autonomy support, and coaching information (regarding training session planning, estimations on player physical activity and lesson context during training, perceived ability to modify training sessions, perceived importance of physical activity during training, intention to increase physical activity/reduce inactivity, and likelihood of increasing physical activity/reducing inactivity) were assessed at baseline (day 1) and at follow-up (day 5). Linear mixed models will be used to analyse between arm differences in changes from baseline to follow-up on all outcomes.

**Discussion:**

The current trial protocol describes, to our knowledge, the first trial conducted in an OYS context to investigate the efficacy of an intervention, relative to a control, in increasing MVPA. This study’s findings will provide evidence to inform strategies targeting coaches to increase MVPA in OYS, which could have major public health implications, given the high proportion of children and adolescents who participate in OYS globally.

**Trial registration:**

This trial is registered with the Australian New Zealand Clinical Trials Registry, ACTRN12613001099718.

## Background

Globally, high proportions of children and adolescents participate in organised youth sports (OYS) [1-3]. In Australia, yearly prevalence data indicate that approximately 69% of children (67% of girls) participate in at least one OYS (including dance) outside of school hours [4]. An array of physical and psychosocial health and developmental benefits are associated with children and adolescents’ participation in OYS including, but not limited to, skill development, muscular strength and endurance, increased self-esteem, and positive peer relationships [5]. Given the high proportion of children who participate in OYS, coupled with myriad health and developmental benefits associated with sports participation, OYS has the potential to be a powerful health-promoting environment for children and adolescents.

One of the most pertinent attributes of OYS is its potential to contribute considerably to levels of moderate-to-vigorous physical activity (MVPA) in children [6,7]. Given that a sizeable proportion of children and adolescents do not meet the recommended 60 minutes of daily MVPA [8-11], participating in OYS could have a major impact on public health outcomes related to activity levels. This is particularly important for girls, as research shows that they are less physically active than boys [8,10], with the most pronounced declines in physical activity participation observed in adolescence [10].

Although OYS may provide an ideal opportunity for children and adolescents to accumulate substantial amounts of MVPA, studies have found that children and adolescents spend large proportions of time during OYS inactive or in light physical activity [6,12,13]. Furthermore, using a direct observation system [14], Guagliano, Rosenkranz, and Kolt [6] observed that coaches spent a considerable proportion of training time managing and instructing their players, time when children and adolescents would be relatively inactive. There is potential, then, for coaches to be able to influence their players’ physical activity levels; particularly during training where coaches are better able to dictate the intensity of physical activity, as compared to during a game. That said, to our knowledge, no study has used coaches to promote physical activity in OYS. One study, however, explored OYS coaches’ perceptions on this topic and it appears that coaches have the potential to be ideal candidates to promote physical activity in OYS [15]. Most coaches in the aforementioned study considered themselves role models for physical activity and felt it was part of their role as a coach to promote a fun, friendly, and supportive team environment that provided players with sport-specific development (physical and tactical skills) [15].

Recently, there has been a call to evaluate strategies for increasing MVPA in OYS [12]. The current trial protocol presents, as far as we are aware, the first randomised controlled trial (RCT) to be conducted in an OYS context aimed at determining the efficacy of coach education on MVPA. The primary aim of this two-armed RCT was to assess whether coaches who attended coach education sessions (where education on increasing MVPA and decreasing inactivity during training was delivered) could increase their players’ MVPA during training sessions over a 5-day basketball program compared to coaches who did not receive coach education sessions. The secondary aims were to: (1) assess whether players who were coached by coaches who have attended coach education sessions spent a lower percentage of time inactive during training sessions compared to players who are coached by coaches who did not attend coach education sessions; and (2) to investigate motivational effects on player physical activity. We also investigated changes in coaches’ awareness of player physical activity, how time was spent during training (lesson context), and leader behaviour.

Compared with a standard-care control coached as normal, we hypothesised that players who have been coached by coaches who have attended coach education sessions will: (1) spend a greater percentage of time in moderate-to-vigorous physically activity, (2) spend a lower percentage of time inactive, and (3) not exhibit lower motivation scores. Also, we hypothesised that coaches who have attended coach education sessions will have a greater awareness of their players’ physical activity.

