### Sample size and power calculation

On the basis of an α of 0.05 and 80% power to detect a significant differential change in MVPA between groups, using an effect size of *d* = 0.6, a minimum sample size of 36 female players for each group was needed (*N* = 72). Our effect size is consistent with the findings of a recent systematic review and meta-analysis of interventions designed to increase children and adolescents’ MVPA in a similar setting (physical education), *d* = 0.62 [18]. To protect against player attrition and preserve adequate statistical power, the sample size was inflated by 10%, thus a total sample of 80 female players was sought.

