#### Questionnaires

At baseline (day 1) and follow up (day 5), players were asked to complete a questionnaire assessing their perceptions of their coach’s autonomy-supportive behaviour by completing 4 items from the Teacher as Social Context Questionnaire [41,42]. Players responded to questions on a 7-point Likert scale (1 = not true at all, 7 = very true). Scores on the TASC were averaged and ranged from 1 to 7, higher scores were indicative of greater perceived coach autonomy-supportive behaviour.

Players also completed the 14-item Situational Motivation Scale which assesses constructs of intrinsic motivation, identified regulation, external regulation, and amotivation [43]. Players responded to questions on a 7-point Likert scale (1 = not true at all, 7 = very true). Based on players’ average scores from the four subscales of the SIMS, a self-determination index (SDI) was created (SDI = 2*intrinsic motivation + identified motivation – external regulation – 2*amotivation, e.g., Lonsdale et al. [44]). Scores on the SIMS can range from −18 to 18, where higher scores were indicative of greater self-determined motivation towards participation in a situation (i.e., basketball practice) [44,45]. Both the Teacher as Social Context Questionnaire and the Situational Motivation Scale have received empirical support for reliability and validity [41,46,47].

A demographic questionnaire was distributed to parents and coaches for descriptive data purposes. The questionnaire that was distributed to parents collected data on parents’ level of education, relationship status, and household income. The questionnaire also collected data on their daughter’s age, country of birth, cultural background, and OYS information (number of OYS played, level, number and minutes of training sessions per week, and number and minutes of games per week). This questionnaire was only distributed to parents once, prior to the commencement of the study.

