### Statistical analysis

All variables will be checked for normality using the Shapiro-Wilk test. Independent samples *t-*tests or Mann–Whitney *U-*tests will then be conducted, as appropriate, to examine: (1) baseline differences between groups and (2) baseline differences between players who completed the study and those lost to follow-up. If variables significantly differ between groups, they will be appropriately adjusted in the main analyses.

Linear mixed models will be used to analyse the differential change between groups on all outcomes from baseline to follow-up, using baseline data as the covariate. Linear mixed models will be used because these models are robust enough to withstand the biases from missing data, and provide good control of Type I and Type II errors [50]. All analyses will be conducted using SPSS 21.0 (Chicago, IL, USA). The level of significance will be set at *p* < 0.05.

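### Hypothesis 3 says motivation will not be lower, but the only stated criterion is a difference test at p < 0.05, which can refute that claim but cannot establish it

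*Protocol article*

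**What the plan says.** In the Background, the first two player hypotheses are directional superiority claims: more time in MVPA and less time inactive. The third is of another kind: intervention players will "not exhibit lower motivation scores" than controls. Motivation belongs to the second of two secondary aims.

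Under Questionnaires, the Situational Motivation Scale is reduced to a self-determination index, on which higher is better: "Scores on the SIMS can range from −18 to 18". It is collected on days 1 and 5.

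The Statistical analysis section has one inferential rule: "Linear mixed models will be used to analyse the differential change between groups on all outcomes from baseline to follow-up", with baseline as the covariate, and "The level of significance will be set at *p* < 0.05". The section does not say whether tests are one- or two-sided. The article states no margin and no confidence-bound criterion for motivation.

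The sample size section concerns MVPA only: "On the basis of an α of 0.05 and 80% power to detect a significant differential change in MVPA between groups".

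**The concern.** A difference test takes no difference as its null hypothesis. Rejecting that null in the unfavourable direction refutes hypothesis 3. Failing to reject it leaves open both no drop and a drop too small for the trial to detect. Under the stated rule, the less precise the trial, the less likely hypothesis 3 is to be contradicted, which is the wrong way round for a claim of no reduction.

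The article's Discussion says that a successful trial will support using coach education sessions to raise MVPA. Whether more active training costs girls some motivation bears on that recommendation. If the plan has no criterion able to support the answer it predicts, the motivation result may be given more weight than it can carry.

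**Working it through.** **Inputs from the article.** α = 0.05; at least 36 players per group; 80 players sought at 1:1, so 40 per arm; baseline used as a covariate.

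**Assumptions, because the article gives no figure.** Differences in SD units of the day-5 index; baseline correlation r of 0, 0.5 or 0.7; two-sided testing, with a one-sided variant; independent players.

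**1. The plan's own figure.** It is "a minimum sample size of 36 female players for each group was needed", obtained "using an effect size of *d* = 0.6". For a two-sample t-test at 80% power, one-sided α = 0.05 needs 35.04 per group, which rounds up to 36, so the figure reproduces. Two-sided α = 0.05 needs 44.6, so it does not. With 36 per group the two-sided power for MVPA is 71%. That is a separate matter, but it shows why sidedness cannot be taken for granted below. No corresponding figure exists for motivation.

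**2. Chance that a real drop is non-significant.** With n per arm, true drop d and residual SD s = √(1 − r²), the noncentrality is (d/s)·√(n/2) on 2n − 2 degrees of freedom. The chance of non-significance is the noncentral t probability between the two-sided critical values. The 95% CI half-width is t(0.975)·s·√(2/n).

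Example with n = 36, r = 0, d = 0.3: noncentrality 0.3 × √18 = 1.273; critical value 1.994; probability 0.759. Half-width 1.994 × √(2/36) = 0.470 SD.

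| Per arm | r | 0.3 SD drop non-significant | 0.5 SD drop non-significant | 95% CI half-width |
|---|---|---|---|---|
| 36 | 0 | 0.759 | 0.447 | 0.47 SD |
| 36 | 0.5 | 0.695 | 0.324 | 0.41 SD |
| 40 | 0.5 | 0.666 | 0.278 | 0.39 SD |
| 40 | 0.7 | 0.542 | 0.129 | 0.32 SD |

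A one-sided 0.05 test for a drop, with 36 per arm and no adjustment, gives 0.650 and 0.324.

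**3. What a margin would demand.** With a true difference of zero and a lower limit from a two-sided 95% CI, power is approximately Φ(m/(s·√(2/n)) − 1.96) for margin m. With 36 per arm:
- r = 0: m = 0.3 SD gives Φ(1.273 − 1.96) = 25%; m = 0.5 SD gives Φ(2.121 − 1.96) = 56%.
- r = 0.5: the same margins give 31% and 69%.

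These margins are illustrations, not proposals.

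**The case against.** **Interpretation.** A reader might infer that the investigators will take p > 0.05 as confirmation of hypothesis 3 and report a real drop as no harm. The article does not say so. It sets a significance level but no rule for concluding on hypothesis 3, and the planned model also yields a difference and a confidence interval that could be read properly. This stands, and the inference should not be stated as fact. It remains true that, apart from a significant gain, which the hypothesis does not predict, the stated rule offers no other way to support it.

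**Documents not shown.** A margin for a secondary outcome is often left to an analysis plan. That is fair for the margin alone. But the article itself assigns a difference test and a threshold to all outcomes, and that rule does not match one of its own hypotheses. The mismatch is in the text shown.

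**Role of motivation.** A reader might treat it as a formal safety check. The article does not call it that. The secondary aim is worded as investigating motivational effects on activity, and the hypothesis is introduced without confirmatory language. This limits the weight of the point.

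**Size.** The 76% and 45% figures ignore the baseline covariate, the 80 players sought and the possibility of one-sided testing. This stands, and is why a range is given.

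**Clustering.** A reader might add that clustering makes all this worse. The article says re-randomising players to coaches each session avoids it, and gives no design effect for the questionnaire. Any loss of power would follow only in a model that accounts for clustering; if clustering were present but unmodelled, the naive test would reject more often at the 0.3 SD drop. The figures here do not rely on it.

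**Conclusion.** The point holds as a mismatch between a stated hypothesis and the only stated criterion: the rule can contradict hypothesis 3 but, short of a significant gain, cannot establish it.

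Under two-sided testing with independent players, a true 0.3 SD drop goes undetected in 54% to 76% of trials and a 0.5 SD drop in 13% to 45%, depending on the assumed n and baseline correlation. The unadjusted one-sided variant with 36 per arm gives 65% and 32%. Even an observed difference of exactly zero would leave drops of 0.32 to 0.47 SD inside the 95% interval. The most favourable row makes a 0.5 SD drop fairly hard to miss, but a 0.3 SD drop would still be missed more often than not.

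All these figures are in assumed SD units, since the article gives no SD for the index. The outcome is secondary, and the MVPA conclusion does not depend on it. The correction should be made, but it does not threaten the trial's main result.

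**What to change.** Before unblinding, choose one of two routes, both using the model already planned:

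- **Margin.** Justify a non-inferiority margin on the self-determination index. Conclude that motivation is not lower only if the lower limit of the two-sided 95% CI for the intervention-minus-control difference lies above minus that margin.
- **Estimation.** Treat hypothesis 3 as an estimate. Report the baseline-adjusted difference with its 95% CI, and state that p > 0.05 is not evidence of no reduction.

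The cost is one or two sentences, plus the work of justifying a margin on the first route. No new data or model is needed. The drawback is that hypothesis 3 may be inconclusive: at the illustrative margins and 36 per arm, power ranges from 25% to 69%. If no margin can be defended, the estimation route is the better choice.

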## Methods/design

### Trial design

This study is a two-armed, parallel-group RCT, using a 1:1 allocation ratio, designed to investigate whether coaches who attended coach education sessions (where education on increasing MVPA and decreasing inactivity during training was delivered) can increase their players’ MVPA during training sessions over a 5-day basketball program; compared to coaches who did not receive coach education sessions (Figure 1). Outcomes were assessed at baseline (day 1 of the basketball program) and follow up (day 5 of the program). The Human Research Ethics Committee of the University of Western Sydney (UWS) approved this study. This study adheres to the Consolidated Standards of Reporting Trials guidelines [16].

**Figure 1 F1:**
[figure not shown]
Flow diagram of study protocol.

### Participants

We planned to recruit a convenience sample of 80 female players and 8 coaches into the UWS School Holiday Basketball Program. Players were recruited through the distribution of flyers to 5 OYS basketball clubs, 6 primary schools (private and Catholic), 3 community centres, 2 after-school programs, and social media (Yammer and E-update, which are private social networks for UWS staff, were used). Coaches were recruited via flyers to 2 OYS basketball clubs and the UWS (undergraduate students). To be considered eligible for this study as a player, participants needed to be female, aged 9–12 years, and intend to attend the program for its duration. For coaches to be eligible to coach in the program, basketball coaching credentials from the Australian Sports Commission’s National Coaching Accreditation Scheme (NCAS) [17] and previous experience coaching girls basketball teams were required. Coaches were also informed that participation might involve attending 2 coach education sessions; however, no information was divulged regarding what the coach education sessions entailed. Coaches also received payment for their time, at a rate of AUD$25/hour (intervention coaches were also paid to attend coach education sessions at the same rate).

### Sample size and power calculation

On the basis of an α of 0.05 and 80% power to detect a significant differential change in MVPA between groups, using an effect size of *d* = 0.6, a minimum sample size of 36 female players for each group was needed (*N* = 72). Our effect size is consistent with the findings of a recent systematic review and meta-analysis of interventions designed to increase children and adolescents’ MVPA in a similar setting (physical education), *d* = 0.62 [18]. To protect against player attrition and preserve adequate statistical power, the sample size was inflated by 10%, thus a total sample of 80 female players was sought.

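### The 36 players per group matches a one-sided 5% calculation; tested two-sided at p < 0.05, the stated inputs give about 71% power for d = 0.6, not 80%

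*Protocol article*

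**What the plan says.** The section on sample size and power gives its inputs in one sentence: "On the basis of an α of 0.05 and 80% power to detect a significant differential change in MVPA between groups", with d = 0.6. It concludes that "a minimum sample size of 36 female players for each group was needed", N = 72 in total. It supports d = 0.6 by a meta-analysis in physical education that found d = 0.62. For attrition, "the sample size was inflated by 10%, thus a total sample of 80 female players was sought". The trial design section adds that the groups are formed "using a 1:1 allocation ratio".

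The statistical analysis section plans a linear mixed model that compares the two arms on change over the program, with the baseline value as covariate. It continues "The level of significance will be set at" p < 0.05. Neither section says whether α is one-sided or two-sided, and the sample size section mentions no correlation between baseline and follow-up. The primary hypothesis at the end of the Background is directional (more time in MVPA under educated coaches), but it is not tied to a one-sided test.

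**The concern.** For a two-group comparison with d = 0.6, α = 0.05 and 80% power, the familiar two-sided answer is about 45 per group, so 36 is too small by 9 per group, which is more than rounding. If the number came from a one-sided calculation while the result is judged by an ordinary two-sided p < 0.05, the planning and the analysis use different tests, and the stated power does not belong to the test that will be reported.

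This is the only power statement for the primary outcome. A reader of a non-significant MVPA result would take the chance of having missed d = 0.6 to be 20%. On the printed inputs it is about 29% with 36 per group.

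**Working it through.** **Inputs.** From the sample size section: d = 0.6 (so SD = 1), α = 0.05, power 0.80, 36 per group, 72 raised to 80 in total. From the trial design section: 1:1 allocation. From the statistical analysis section: p < 0.05, baseline as covariate.

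**1. Reproducing the stated 36.** The normal approximation is n per group = 2(z_α + z_power)² / d², with z_power = 0.842.

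- One-sided 5%: 2(1.645 + 0.842)² / 0.36 = 34.3, so 35.
- Two-sided 5%: 2(1.960 + 0.842)² / 0.36 = 43.6, so 44.

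The exact calculation uses the noncentral t distribution with 2n − 2 degrees of freedom and noncentrality d√(n/2):

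| Test | d | n solved | n per group |
|---|---|---|---|
| One-sided 5% | 0.60 | 35.04 | **36** |
| Two-sided 5% | 0.60 | 44.59 | 45 |
| One-sided 5% | 0.62 | 32.87 | 33 |
| Two-sided 5% | 0.62 | 41.82 | 42 |

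The stated 36 is reproduced exactly by the one-sided t calculation at d = 0.6. No two-sided calculation on the printed inputs comes near it, even with the cited d = 0.62.

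**2. Power of a two-sided 5% test at the planned sizes.** With 36 per group, the noncentrality is 0.6 × √18 = 2.546, against a critical value of 1.994 on 70 degrees of freedom. With 40 per group it is 0.6 × √20 = 2.683, against 1.991 on 78.

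| n per group | Two-sided power, d = 0.6 | One-sided power, d = 0.6 | d detectable with 80% two-sided power |
|---|---|---|---|
| 36 | 70.9% | 80.9% | 0.67 |
| 40 | 75.5% | 84.5% | 0.63 |

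The attrition step is correct (72 / 0.9 = 80), but it does not close the gap: with no losses at all, two-sided power is still 75.5%. Evaluable data on 90 players would need 90 / 0.9 = 100 recruited.

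**3. Possible gain from baseline adjustment.** The article gives no correlation r between day 1 and day 5, so r is an assumption here. If d = 0.6 is on the raw-SD scale, adjustment shrinks the residual SD to √(1 − r²), and the effective d becomes 0.6 / √(1 − r²). Two-sided power is then:

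| r | 36 per group | 40 per group |
|---|---|---|
| 0 | 70.9% | 75.5% |
| 0.3 | 74.9% | 79.3% |
| 0.5 | 82.6% | 86.4% |
| 0.7 | 94.0% | 96.0% |

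Power reaches 80% at r of about 0.44 (36 per group) or 0.32 (40 per group). For an unadjusted comparison of change scores, whose SD is √(2(1 − r)), 36 per group reaches 80% only at r of about 0.60; at r = 0.3 it gives 56.4%.

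**The case against.** The strongest reply is that the planned analysis is adjusted for baseline, so the 71% describes a simple t-test that nobody intends to run. With d on the raw-SD scale and r near 0.45, a two-sided 5% test also leads to about 36 per group, as does a change-score comparison with r near 0.60. The one-sided origin is then an inference from a numerical match, and 71% is the floor of a range for the adjusted analysis before any clustering. This stands as a caution about cause: the article does not prove how 36 was obtained. It does not rescue the paragraph, because the sample size section names no correlation, claims no such gain, and attaches d to the differential change itself, in which case the gain may already be included in d.

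A second reply is that the hypothesis is directional and sidedness is undeclared rather than contradicted. If a one-sided 5% test was meant, 36 per group gives 80.9% and the arithmetic is right. But a directional hypothesis is not a declared one-sided test, and the same p < 0.05 governs every outcome. Intending a one-sided 5% test would also double the usual false-positive allowance in the favourable direction, which would have to be said openly.

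A third reply is that a condensed article may leave such detail to the full protocol. That would excuse an omission. Here the article prints its inputs and a result, and the result does not follow from them under the conventional test.

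**Conclusion.** The point holds. On the inputs printed, 36 per group gives 80% power only for a one-sided 5% test. For the conventional two-sided test at p < 0.05, power to detect d = 0.6 is 70.9% at 36 per group and 75.5% at 40, and the size needed is 45 per group.

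These figures assume independent players, equal groups, and d = 0.6 on the scale of the quantity actually compared. A raw-scale d with a baseline correlation of at least about 0.44 (36 per group) or 0.32 (40 per group) would bring power back to 80%, but the article does not state or claim this. Any correlation between players trained by the same coach or in the same session would lower power further, and it is left out of every figure here. The planned estimate and its test are not affected; the error is in the power claimed for them.

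**What to change.** Rewrite the sample size paragraph so that it states that the primary test is two-sided at 0.05, says on which scale d is expressed, and gives the power that follows. Without credit for baseline adjustment, the wording could be: *at two-sided α = 0.05, 36 players per group give 71% power for d = 0.6 (75% with 40 per group); 80% power is available for d = 0.67 with 36 per group (0.63 with 40).* If baseline adjustment is credited, give the assumed day 1 to day 5 correlation, its source, and the power it yields. If a one-sided test was intended, say so in both the sample size and the statistical analysis sections and justify it.

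The cost is one paragraph and a less favourable power figure. No extra players or procedures are needed; the program ran in September 2013, so the sample size itself can no longer change.
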